### Measurements of cognitive function

2.9

#### Short-term VR intervention trial

2.9.1

The DSST and BDS tests have been widely used in the field of VR environments for cognitive function, and they are highly responsive to the immediate effects of short-term interventions (Liu et al., 2022; Yin et al., 2018). Therefore, cognitive function is assessed by DSST (score range: 0–90) and BDS (score range: 0–9) scales. The DSST test is a simple and fast assessment tool that measures the ability to link symbols with numbers in 90 s (Beres and Baron, 1981). The DSST score is the number of symbols correctly filled in consecutively within 90 s. In the BDS scale, testing begins with three-digit numbers, which are read aloud to the participant, who is then required to repeat them in reverse. The test progresses sequentially to nine-digit numbers, with each sequence allowing up to two attempts. If a participant fails to correctly repeat a sequence of a specified length twice consecutively, the test is stopped. The number of digits in the longest correctly repeated sequence serves as the measure of cognition.

#### Long-term real environment intervention trial

2.9.2

Cognitive scores will be derived from the DSST and MoCA scales (score range: 0–30). The MoCA can track gradual, multidimensional cognitive decline over extended periods, complementing DSST’s focus on processing speed—a domain particularly impaired in diabetes-related cognitive dysfunction (Li et al., 2023; Rawlings et al., 2015). The DSST score measurement is the same as in the short-term trial. The MoCA is a brief cognitive screening tool with high sensitivity in detecting MCI (Nasreddine et al., 2005). It measures several cognitive domains, including attention, memory, delayed recall, language, executive function, abstraction, and orientation to time and place (Bischoff-Ferrari et al., 2020). The MoCA consists of 30 questions, and the score is equal to the number of correct answers out of the 30 items. If the individual reports 12 years of education or less, an additional point is added.

### Randomization

2.10

Randomization is conducted by a computer-generated list of random numbers made by independent statisticians without any clinical involvement in the study. The block randomization sequence is generated using SAS 9.4 software (PROC PLAN). The randomized block sizes are set to 8 and 16 for the short-term VR intervention trial and 2 and 4 for the long-term real environment intervention trial. After obtaining eligible patient consent, allocations are determined using sequentially numbered sealed envelopes containing information disclosing the type of intervention to be applied. Additionally, group assignments will be concealed until the intervention begins.

### Sample size

2.11

#### Short-term VR intervention trial

2.11.1

The randomized block analysis of the variance module of PASS 11.0 was used to calculate the sample size. According to previous literature (Liao et al., 2020), the MoCA scores would increase by 0.5 points, and the Chinese version of the Verbal Learning Test (CVVLT) immediate recall scores would increase by 1.0 point after VR intervention. The DSST has been found to be more sensitive than the MoCA and CVVLT. Thus, we conservatively assumed that the mean difference in DSST scores between the intervention and control groups would be 1.0, with a standard deviation of 1.2. The number of blocks was set at 8, the significance level was set at *p* < 0.05 and the statistical power was set at 90%. Based on the above parameters, the minimum sample size per block is six individuals. Considering the possibility of noncompliance or refusal to participate, the sample size was increased by 20%, resulting in eight individuals per block. Thus, there are eight blocks in the short-term trial, with each block containing eight individuals.

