#### Short-term VR intervention trial

2.12.1

The analysis will be carried out according to the intention-to-treat principle. Given the short duration of this trial, missing data is expected to be minimal. Therefore, a single imputation will be used to process the incomplete data. Outliers will be identified using the interquartile range (IQR) method, defined as values below Q1 − (1.5 × IQR) or above Q3 + (1.5 × IQR), and will be replaced with Q1 − (1.5 × IQR) and Q3 + (1.5 × IQR), respectively. One-way analysis of variance (ANOVA) (for continuous and normally distributed variables) and chi-square test (for categorical variables) will be conducted to assess the baseline equivalence between the eight groups. If there are differences in characteristics between groups at baseline, the differences will be adjusted by performing multiple linear regression. ANOVA will be used to compare whether there are statistically significant differences in cognitive scores, heart rate and blood pressure among the eight groups. For each group, paired *t*-tests will be conducted to examine whether changes in cognitive scores, heart rate, and blood pressure are statistically significant between baseline, pre-intervention, and post-intervention. The identification of optimal biophilic elements will follow a two-stage analytic protocol. First, multiple linear regression models adjusted for covariates will be fitted to compare post-VR intervention cognitive scores between each intervention group and the control. Groups achieving a covariate-adjusted *p* < 0.1 in these pairwise comparisons will be considered statistically promising. Subsequently, among these candidate groups, the intervention demonstrating the largest adjusted mean difference in cognitive scores relative to the control group will be selected for long-term real environment intervention. Multiple linear regression will be used to evaluate the cognitive improvement in each group after adjusting for covariates. Continuous variables will be assessed for normality prior to analysis. If the data are not normally distributed, the Kruskal-Wallis H test will be used to compare the differences between the eight groups.

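### The short-term sample size states 90% power for a DSST difference of 1.0 with SD 1.2, but neither number has a basis on the DSST scale

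*Protocol article*

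**What the plan says.** Section 2.11.1 (short-term trial) begins with two results from earlier literature: "the MoCA scores would increase by 0.5 points", and on the Chinese verbal learning test (CVVLT), "immediate recall scores would increase by 1.0 point after VR intervention". It links them to this trial's outcome in one sentence: "The DSST has been found to be more sensitive than the MoCA and CVVLT". From that it concludes: "we conservatively assumed that the mean difference in DSST scores between the intervention and control groups would be 1.0, with a standard deviation of 1.2". With 8 blocks, significance at 0.05 and 90% power, it reports a minimum of 6 per block, raised to 8 for non-compliance, giving 64 in total.

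Section 2.9.1 defines the outcome: "cognitive function is assessed by DSST (score range: 0–90) and BDS (score range: 0–9) scales". The DSST score is a count of symbols completed in 90 seconds. Section 2.12.1 then uses covariate-adjusted linear regression to "compare post-VR intervention cognitive scores between each intervention group and the control". Scenes with p<0.1 become candidates, and the candidate with the largest adjusted mean difference goes into the 24-month trial.

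**The concern.** Both inputs to the power calculation must be on the scale of the outcome and of the contrast analysed. Here the difference is taken from gains on two other tests, and the SD comes with no source. Being more sensitive does not turn a point on one instrument into a point on another, and it says nothing about how widely DSST scores vary between people.

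The SD matters most. It fixes the signal-to-noise ratio of the comparison that chooses the long-term intervention. If the relevant DSST SD is several points rather than 1.2, a true 1-point benefit would seldom cross p<0.1 with 8 per arm, and the ranking by largest difference would owe much to chance. Repairing the sample-size formula while keeping 1.0 and 1.2 would still leave a power statement with no DSST basis.

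**Working it through.** **Inputs.** From 2.11.1: difference 1.0, SD 1.2, alpha 0.05, power 90%, and 6 raised to 8 per block. From 2.12.1: scene-versus-control comparisons with a p<0.1 threshold. From 2.12.2: two-tailed tests. From the abstract: 64 participants in eight groups, so 8 per arm. No DSST SD is given; SDs of 3, 5 and 10 below are assumptions that show a range.

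**1. The plan's own figure.** For one scene against control, n per arm = 2(1.96 + 1.282)² × (1.2/1.0)² = 2 × 10.51 × 1.44 ≈ 30.3, so 31 (32 by the exact t distribution). The stated 6 is not reproduced: exact-t power with 6 per arm is 26%. The 8-group F test with control at 0 and the seven scenes at +1 has 19–20% power at 6 per group and about 27% at 8. The step from 6 to 8 is sound (6/0.8 = 7.5, rounded up). This mismatch is a separate formula problem, reported here only so that the two are not confused.

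**2. What an SD of 1.2 implies.** Under normality, 95% of scores lie in a band of width 2 × 1.96 × 1.2 = 4.7 symbols on a 0–90 scale. Section 2.4.1 admits anyone aged 60 or older, with no upper age limit and no restriction on education.

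**3. When 1.2 could be right.**
- As a residual SD given the pre-intervention score: r = √(1 − (1.2/SD)²). For a raw SD of 5, √(1 − 0.0576) = 0.971. For a raw SD of 10, √(1 − 0.0144) = 0.993.
- As a change-score SD with equal variances: r = 1 − (1.2/SD)²/2. For SD 5 this is 0.971; for SD 10, 0.993.

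Either reading needs a very high pre–post correlation if the raw SD is 5 or more. At a correlation of 0.9, a residual SD of 1.2 corresponds to a raw SD of only 1.2/√(1 − 0.81) = 2.75.

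**4. Power over the assumed range.** Two-sample t-test, 8 per arm, 14 degrees of freedom, both tails. Noncentrality = 1.0/(SD × √(2/8)) = 2/SD.

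| SD | Noncentrality | Power at 0.05 | Power at p<0.1 |
|---|---|---|---|
| 1.2 (plan) | 1.667 | 34% | 48% |
| 3 (assumed) | 0.667 | 10% | 17% |
| 5 (assumed) | 0.400 | 7% | 12% (0.1245) |
| 10 (assumed) | 0.200 | 5% | 11% |

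Pooling the error over all eight arms (56 degrees of freedom) changes little: 37% and 50% for SD 1.2, 10% and 17% for SD 3.

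**5. Detectable difference.** For 90% power at 0.05 with 8 per arm, the standardised difference is about 1.74 (14 degrees of freedom) or 1.65 (56). At about 1.74 SD, that is 2.1 points if the SD is 1.2, 5.2 if 3, 8.7 if 5, and 17 if 10.

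**The case against.** The strongest defence has four parts.

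- **A floor argument.** If the DSST responds more than both cited tests, its effect should be at least the larger gain, so 1.0 is a floor. This is coherent only if the points are comparable across scales, which the protocol does not show, and it supplies no SD.
- **The SD may not be a raw SD.** The paired tests in 2.12.1 make a change-score SD a possible reading, and the covariate-adjusted regression allows a residual SD. This stands as a possibility, but 2.11.1 does not say so and the implied correlation is very high.
- **The size of the loss is assumed.** Correct. The document contains no DSST mean or SD, so the figures for SD 3, 5 and 10 are illustrations.
- **The trial is already a screen.** The Introduction describes it so, and the choice is tested afterwards in a separate randomised trial of 240. A poor choice could therefore cost that trial its opportunity but would not bias its comparison.

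Several stronger readings are tempting and go beyond the text. A reader might infer that 1.2 was copied from the MoCA or CVVLT results; the protocol states no origin for it. A reader might say 0.5 was the truly conservative choice, but that again treats a MoCA point as a DSST point. A reader might argue that the cited gains are within-person changes that include practice effects shared by controls, who also repeat the DSST (2.5.1). The wording allows this, but it does not establish whether the cited results are changes or between-arm contrasts. Finally, a reader might say that a useful scene passes no more often than a useless one. That nearly fits SD 10 (11% against 10%) but not SD 3 (17% against 10%).

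**Conclusion.** The point holds in this form: 2.11.1 gives no DSST-scale support for the difference or the SD, the word *conservatively* is unsupported, and the 90% figure does not describe the comparison of 0–90 DSST scores that the trial makes. An SD of 1.2 is implausible for raw post-VR scores. That is a judgement from the 4.7-symbol band and the broad eligibility, not a figure in the document. If the relevant SD lies between 3 and 10, power for a 1-point difference is 5–10% at 0.05 and 11–17% at p<0.1. The 34% and 48% obtained from the plan's own inputs belong to the separate formula problem and should not be counted as the effect of this one. The consequence is an overstated ability to pick the right scene. It does not invalidate the later trial.

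**What to change.** In 2.11.1:

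- Delete *conservatively* and the transfer from the MoCA and CVVLT.
- State a DSST SD that matches the analysis: the residual SD given the pre-intervention DSST if the model adjusts for it, otherwise the raw post-VR SD. Take it from DSST data, or estimate it arm-blind as the short-term data accrue.
- If it is arm-blind, note that it includes any between-arm differences. The inflation is small here: with the seven scenes 1 point above control, the between-arm variance is (7/8)(1/8) = 0.109, which moves an SD of 3 to √9.109 = 3.02.
- Keep N at 64. Replace the 90% power statement with the DSST difference that 8 per arm can detect (about 1.7 SD for 90% power at 0.05) and the power at the p<0.1 threshold.

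The cost is one SD estimate and a rewritten paragraph, with no extra participants and no change to the selection rule. The downside is that the stated power becomes less favourable.

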#### Long-term real environment intervention trial

2.12.2

The modified intention-to-treat population (mITT) will be used for statistical analysis. Missing values will be imputed using multiple imputation. Firstly, two sample t-tests (for continuous and normally distributed variables) and chi-square test (for categorical variables) will be conducted to assess the baseline equivalence between the intervention and control groups. Two sample t-tests will be used to compare whether cognitive scores are statistically different between two groups. Multiple linear regression will be used to demonstrate whether the intervention is statistically associated with cognitive scores after adjusting for potential confounders. Repeated measures ANOVA will be used to compare cognitive scores across groups. The potential confounders will be corrected in the mixed-effect model to determine the association between intervention and cognitive scores. If the intervention has a direct effect on cognitive function, longitudinal causal mediation analysis will be further used to clarify the mediating factors through which the intervention may affect cognition.

To explore the interaction of *APOE4* and the biophilic environment on cognition, we will perform stratified analysis according to groups to clarify the main effects of *APOE4* on cognitive function. Then, mixed models will be used to adjust for potential covariates and to elucidate the main effect of *APOE4* on cognitive function in each group. Finally, the interaction term between the *APOE4* and the intervention group will be included in the mixed-effects model to identify the effect of the genetic-environmental interaction on cognitive function.

In our study, all statistical tests are two-tailed, with a significance level of *p* < 0.05.

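### The short-term trial's 90% power claim does not follow from its own inputs: scene versus control has 37% power at 0.05, or 50% at the p<0.1 selection threshold, with 8 per arm

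*Protocol article*

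**What the plan says.** Section 2.11.1 (Sample size, short-term trial) uses a randomised-block ANOVA module. It says "we conservatively assumed that the mean difference in DSST scores between the intervention and control groups would be 1.0, with a standard deviation of 1.2". It adds "The number of blocks was set at 8" and "the significance level was set at *p* < 0.05 and the statistical power was set at 90" per cent. It concludes: "Based on the above parameters, the minimum sample size per block is six individuals". A 20% allowance raises six to eight, giving eight blocks of eight, or 64 people. The Abstract and section 2.1 place these 64 in seven intervention groups and one control group.

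Section 2.12.1 chooses the long-term intervention in two steps. Covariate-adjusted regressions are fitted "to compare post-VR intervention cognitive scores between each intervention group and the control", and scenes with p<0.1 go forward. Among those, the scene with the largest adjusted difference from control is taken. The same section also plans an ANOVA across the eight groups. The last line of section 2.12.2 says that in this study "all statistical tests are two-tailed, with a significance level of *p* < 0.05".

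**The concern.** A standardised difference of 1.0/1.2 = 0.83 is large, but six people per arm is very few for a two-arm comparison at 90% power. If the claim fails, readers are told that an effective scene will rarely be missed when it will often be missed. A scene that does not reach the threshold could then be reported as ineffective. The stage also fixes what 240 people receive in the 24-month trial, so its ability to find the right scene should be stated correctly.

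**Working it through.** **Inputs.** Section 2.11.1 gives difference δ = 1.0, SD σ = 1.2, α = 0.05, power 90%, eight blocks, and six per block raised to eight. Two-sided testing is from section 2.12.2. The selection threshold p<0.1 is from section 2.12.1. Whatever "block" means, 6 × 8 = 48 and 8 × 8 = 64 people over eight arms give n = 6 and n = 8 per arm. Equal allocation is inferred from 64/8.

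**Step 1: try to reproduce six.** By the normal approximation,

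n per arm = 2(1.96 + 1.2816)² σ²/δ² = 2 × 10.51 × 1.44 = 30.3, so 31.

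The noncentral t gives 31 with error pooled over eight arms, or 32 with only the two arms' error. Six is not reproduced. The inflation step is sound: 6/0.8 = 7.5 and 6 × 1.2 = 7.2 both round up to 8.

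**Step 2: power of scene versus control.** Noncentral t with noncentrality (δ/σ)√(n/2) and pooled error df = 8n − 8.

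| n per arm | Noncentrality | df | Power, two-sided 0.05 | Power, p<0.1 |
|---|---|---|---|---|
| 6 | 0.833 × √3 = 1.443 | 40 | 29% | 41% |
| 8 | 0.833 × √4 = 1.667 | 56 | 37% | 50% |

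With only the two arms' error, power at 0.05 is 26% and 34%. With 8 per arm, 90% power needs a difference of 1.65 SD at 0.05 or 1.48 SD at 0.1, which at SD 1.2 is about 2.0 or 1.8 points. At p<0.1, a 1.0-point difference needs 25 per arm.

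**Step 3: covariate adjustment.** If 1.2 is an unadjusted SD, a baseline correlation ρ reduces it to 1.2√(1 − ρ²). The protocol gives no ρ. For an assumed range of 0.3 to 0.7, power with 8 per arm is 40% to 63% at 0.05 and 53% to 75% at p<0.1.

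**Step 4: the eight-group ANOVA.** Noncentrality is n × Σ(mean − grand mean)²/σ², with 7 and 8n − 8 df.

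- All seven scenes 1.0 above control: the sum of squares is 7/8, so the noncentrality is 3.65 (n = 6) or 4.86 (n = 8). Power is 20% and 27%.
- Most favourable pattern with means spanning 1.0 (four arms high, four low): the sum of squares is 2, so the noncentrality is 8.33 or 11.11. Power is 44% and 61%.

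**Step 5: the selection rule itself.** This was simulated at the plan's inputs, unadjusted, with 8 per arm, a p<0.1 gate and then the largest difference.

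- One scene 1.0 better, six equal to control: that scene is selected about 47% of the time.
- All seven 1.0 better: at least one passes about 87% of the time.
- None better: some scene still passes about 20% of the time.

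**Step 6: readings that come near 90%.**

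- Splitting the whole sample into two halves gives 80% for 24 v 24 (88% one-sided) and 91% for 32 v 32.
- Reading 1.0 as the SD of the eight means gives about 99% with six per arm.

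Neither matches the text. Section 2.12.1 plans no two-half comparison, and section 2.11.1 calls 1.0 the mean difference between intervention and control. The second reading could point to a mis-entered input, but the article does not show it.

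**The case against.** Four objections deserve weight.

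**37% is not the power of the actual decision.** This stands. Selection uses a covariate-adjusted p<0.1, where power is 50% with 8 per arm and higher if adjustment reduces the residual SD. No single figure is the true power, so both thresholds and the residual-SD condition must be given. Nothing in the assumed range reaches 90%.

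**Pairwise power is not how a selection stage should be judged.** This stands in part. A reader might infer that the choice of scene is driven mainly by noise, or that most effective scenes will be missed. The plan's inputs do not support that. A lone effective scene ranks top about 82% of the time, and when any scene passes the gate it is the one chosen about 89% of the time. The weakness is narrower: the gate stops that scene from being selected in about half of trials.

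**Pooling arms by element would recover the power.** A reader might take the 91% for 32 v 32 as a rescue. It is not a planned analysis, and it requires each element to have a 1.0-point effect averaged over the others. If all seven scenes are equally 1.0 above control, an element's main effect is only 0.25 point (1.0 with the element, 0.75 without) and power is 13%.

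**Eight blocks of eight is a valid complete-block design.** True, and it is compatible with the randomisation block sizes of 8 and 16 in section 2.10. It is tempting to say that the section writes block where it means arm, but that is an inference. The text is unclear because a minimum of six per block cannot hold eight treatments. Likewise, the text does not say that the SD comes from the MoCA and verbal-learning gains. Those gains support the difference of 1.0, and the SD has no stated source.

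**Conclusion.** Wrong as written. The stated 90% becomes 29% (6 per arm) to 37% (8 per arm) at two-sided 0.05, and 41% to 50% at the p<0.1 selection threshold. The planned ANOVA does not reach 90% for any pattern of means spanning 1.0. These figures assume the plan's 1.0-point difference, a residual SD of 1.2, equal arms and error pooled over eight arms. A multiplicity adjustment for seven comparisons, which the plan does not mention, would lower them. The defect is in the stated power. It does not show that the stage is useless for choosing a scene.

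**What to change.** In section 2.11.1:

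- Replace the 90% statement with: with 8 per arm, residual SD 1.2 and a 1.0-point difference, each scene-versus-control comparison has about 37% power at two-sided 0.05 and about 50% at the p<0.1 selection threshold; 90% power requires a difference of about 1.65 SD (0.05) or 1.48 SD (0.1).
- Describe the short-term trial as a selection (pilot) stage, so that a scene missing the threshold is not reported as ineffective.
- State whether the six and the eight are per arm or per block.
- Give a DSST source for the SD of 1.2, or drop the word describing the assumption as conservative.

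The cost is wording and a lower stated power. No participants are added and the design does not change.

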#### Long-term real environment intervention trial

2.11.2

The randomized block analysis of the variance module of PASS 11.0 was used to calculate the sample size. Due to the lack of long-term longitudinal studies on the impact of biophilic living environments on the MoCA scores in elderly diabetic patients, we referred to studies on the impact of natural environments on cognitive scores. Changes in cognitive scores ranged from 0.020 to 0.029 for each interquartile range shift in the Normalized Difference Vegetation Index (NDVI) (De Keijzer et al., 2018). Based on these findings, we set the between-group difference in cognitive scores at 0.02, with a standard deviation of 0.017, an intraclass correlation coefficient of 0.02, and the number of blocks was set at 2. With these parameters, achieving a statistical power of 90% at the 0.05 level of two-sided significant difference requires 99 participants per group. Accounting for about 20% loss to follow-up, each group will initially need to enroll at least 120 participants, totaling 240 participants across both intervention and control groups. Considering that our participants are older adults, the likelihood of noncompliance is higher than others. Therefore, we chose a 20% non-compliance rate to ensure the study has sufficient statistical power.

Furthermore, the logistic regression module of PASS11.0 was used to calculate the sample size required for analyzing the association between the *APOE4* genotype and cognitive function. According to previous research, the prevalence of MCI in Chinese people aged 60 years and older is about 15% (Jia et al., 2020), the odds ratio of the association between *APOE4* and cognitive impairment in the Chinese population was about 2.5 (Jiang et al., 2017), the *R*^2^ of *APOE4* with other covariates, such as age and gender, is about 0.05, with the significance level was set at 0.05. Based on these parameters, achieving a power of 90% in a two-sided test requires 103 participants. In summary, the long-term trial will include at least 120 subjects in each group.

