**Figure 1 fig1:**
[figure not shown]
Study flow chart. VR, virtual reality; A, natural decorative paintings; B, indoor potted plants; C, ornamental fish.

As for the short-term VR intervention trial, a total of 64 participants over 60 years old with diabetes are recruited. The participants are randomly assigned to seven intervention groups or a control group using block randomization with randomly selected block sizes. The main objective of the short-term trial is to determine which biophilic elements or their combinations show the most significant improvement in cognitive function.

As for the long-term real environment intervention trial, a total of 240 participants over 60 years old with diabetes will be recruited. The participants will be randomly assigned in a 1:1 ratio to either the intervention or control group. The main objectives of this long-term trial are to provide evidence for the healing effects of biophilic environments on cognition, and whether the *APOE4* genotype will modify the healing effects of biophilic environments on cognition in elderly diabetes.

Enrollment completion and final study visit are projected for December 2024 and December 2026, respectively.

This study was approved by the Ethics Committee of Capital Medical University (Approval No: Z2023SY019) and is conducted according to the ethical standards of the Helsinki Declaration. The study protocol was developed according to the Standard Protocol Items: Recommendations for Interventional Trials (SPIRIT) checklist.

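### The long-term trial's 99 per group for 90% power does not follow from its stated inputs for an individually randomised trial, and those inputs cannot describe MoCA or DSST scores

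*Protocol article*

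**What the plan says.** Section 2.11.2 of the protocol article names the randomised block analysis of variance module of PASS 11.0. For lack of long-term studies of biophilic homes and MoCA, it borrows from a study of outdoor greenness, in which cognitive scores changed by 0.020 to 0.029 per interquartile range of a vegetation index. The scale of those scores is not given. From this, "we set the between-group difference in cognitive scores at 0.02, with a standard deviation of 0.017, an intraclass correlation coefficient of 0.02". Two blocks are assumed as well. With 90% power this "at the 0.05 level of two-sided significant difference requires 99 participants per group". Allowing about 20% for loss to follow-up, the plan enrols 120 per group, 240 in all. The same paragraph then calls the 20% a non-compliance rate.

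The design is given in sections 2.1 and 2.10. "The participants will be randomly assigned in a 1:1 ratio to either the intervention or control group", in permuted blocks of 2 and 4. The cognitive primary outcomes (section 2.8.2) are DSST and MoCA. For MoCA (0–30), "the score is equal to the number of correct answers out of the 30 items", plus one point for 12 years of education or less (section 2.9.2). DSST (0–90) counts symbols filled in correctly (section 2.9.1). For the short-term trial, section 2.11.1 assumes a DSST difference of 1.0 with SD 1.2.

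**The concern.** Two things do not fit. First, a difference of 1.18 SD is very large, and an ordinary two-arm trial needs few participants to detect it, yet the plan arrives at 99 per group. An intraclass correlation belongs to a design with clusters, and none is described. Second, 0.02 with SD 0.017 is not on the scale of either cognitive outcome.

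At stake is the meaning of the 90% power claim for the trial's main comparison. As written, it is tied to no MoCA or DSST effect that could occur, so a reader cannot tell what size of effect the trial was planned to detect.

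**Working it through.** **Inputs (section 2.11.2).** Difference δ = 0.02, SD σ = 0.017, ICC ρ = 0.02, two blocks, two-sided α = 0.05, power 90%, stated result 99 per group. Standardised difference d = 0.02/0.017 = 1.176.

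**Step 1: reproduce the 99.** Take a cluster-randomised t-test with K = 2 clusters per arm and m participants per cluster. In SD units, SE = √{2[1 + (m − 1)ρ]/(Km)}, with 2(K − 1) = 2 degrees of freedom (critical value 4.303). Power comes from the noncentral t with noncentrality d/SE.

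- m = 98: SE = √(2 × 2.94/196) = 0.1732, noncentrality 6.792, power 0.8998.
- m = 99: SE = √(2 × 2.96/198) = 0.1729, noncentrality 6.804, power 0.9005.

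So 99 is the smallest m that reaches 90%. In this formula it is the size of one cluster, which means 198 per arm. If there really were two clusters per arm and 99 per group (49.5 per cluster), power would be 0.826.

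**Step 2: the design that is described.** For two individually randomised arms, noncentrality = d√(n/2) with 2n − 2 degrees of freedom.

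- n = 16: power 0.896.
- n = 17: power 0.914.

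The normal approximation gives n = 2(1.960 + 1.282)²/1.176² = 15.2, so 16. A randomised-block F test with two blocks, the kind of module the protocol names, gives 18 per arm (power 0.929). None of these is near 99. At 99 per arm the stated inputs would give power above 99.99%.

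**Step 3: the scale.** Each participant's MoCA or DSST score is a whole number. If all scores were equal except for a proportion p one point away, the SD would be about √p. An SD of 0.017 then means p = 0.017² = 0.000289, about 1 participant in 3,460. The protocol's own short-term DSST SD of 1.2 is about 70 times larger (1.2/0.017 = 70.6). If 0.02 is instead read as a fraction of an SD, power at 99 per arm is about 5%, no more than the significance level.

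**Step 4: what the trial can detect.** Two-sample t-test of one score, two-sided 0.05:

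| Evaluable per arm | 90% power | 80% power |
|---|---|---|
| 96 (120 × 0.8) | 0.470 SD | 0.406 SD |
| 99 | 0.463 SD | 0.400 SD |
| 120 | 0.420 SD | 0.363 SD |

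At 96 per arm, 0.470 SD is 0.9, 1.4 or 1.9 MoCA points if the SD is 2, 3 or 4 (assumed; the document gives no MoCA SD). With adjustment for baseline at an assumed correlation of 0.7, it becomes 0.470 × √(1 − 0.7²) = 0.34 SD.

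**Step 5: the allowance for loss.** 99/0.8 = 123.75, so 124 per arm would be needed. The 120 appears to come from 99 × 1.2 = 118.8, rounded up. After 20% loss, 96 remain. For the 0.463 SD effect, power at 96 is 89.1% instead of 90.0%.

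**The case against.** The protocol names a randomised-block module and never mentions clusters. A reader might infer from Step 1 that a cluster formula was certainly used. The document does not establish this. The match is exact and uses every stated input, but it also requires that a per-cluster figure was reported as per group, and only a limited set of alternatives was tried. It remains a probable explanation, and the finding does not need it: Step 2 stands whichever module was run.

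The borrowed 0.02 may be on a standardised or composite scale, and section 2.9.2 does speak of cognitive scores derived from the two tests. The source's scale cannot be seen, so the 1-in-3,460 figure applies only if 0.017 is meant in raw points. But a score standardised to unit SD would not have an SD of 0.017 either, and the protocol offers no conversion to MoCA or DSST.

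The attrition point is small. The text says about 20% and at least 120, 99 of 120 allows 17.5% loss, multiple imputation is planned, and the shortfall costs about one percentage point of power.

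Two stronger readings are tempting. One is that 240 is too few; nothing here shows that, and on the protocol's own inputs 17 per arm would suffice. The other is that a null result could not be interpreted; it could, from its estimate and confidence interval. Nor can a power loss from non-compliance be quantified, because the protocol does not say how non-compliance would dilute the effect.

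**Conclusion.** Wrong as written. The stated inputs need about 17 per arm (16 to 18 across the methods tried) for the individually randomised design, not 99, and they cannot describe a difference in MoCA or DSST points. The claim of 90% power is therefore unsupported. What the trial does have is 90% power for about 0.47 SD on a single cognitive score with 96 evaluable per arm. This assumes an unadjusted comparison at two-sided 0.05 and 20% loss. It does not cover the five primary outcomes jointly. The conclusion rests on arithmetic and on the scales in the document; only the conversion to MoCA points and the baseline-adjusted figure use outside assumptions. Conduct and validity of the trial are unaffected. The error lies in what readers are told about power.

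**What to change.** Keep 240 participants. In section 2.11.2, delete the calculation built on 0.02, 0.017, the ICC and two blocks. State instead, on one basis throughout, that 96 evaluable per arm (120 less 20% loss) gives 90% power for 0.47 SD and 80% for 0.41 SD, for a single cognitive score at two-sided 0.05. Convert this to MoCA and DSST points with the blinded pooled baseline SD, and say whether an effect of that size is plausible. If the primary analysis adjusts for baseline, give that figure at the same 96 per arm (about 0.34 SD at an assumed correlation of 0.7).

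As a minor correction, drop the claim that 120 secures 99 after 20% loss, and label the 20% as loss to follow-up or as non-compliance, not both.

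The cost is rewording, with no extra participants. The stated detectable effect becomes less favourable.
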